### Study outcomes

2.8

Table 4 shows the primary and secondary outcomes, including the measurement. The secondary objectives/outcomes will be measured using the validated questionnaires at five time-points.

**Table 4. T4:** Summary of the study outcomes and measures.

Outcomes	Description	Measure
Primary	To develop, validate and implement the structured Integrated Emotional-Self Enhancement Program	The researcher has developed a structured program keeping in mind the work structure and stress the nurses might feel in the work and personal environment. The developed program has been validated by the experts who are specialized from the field of nursing management, psychologists, psychiatrists, emotional intelligence, and human resources.
Secondary 1	To determine the impact of Integrated Emotional-Self Enhancement Program on staff nurses’ emotional intelligence	GENOS Emotional Intelligence Inventory (Concise version) ( Palmer, Stough, Harmer, & Gignac, 2009).
Secondary 2	To determine the impact of Integrated Emotional- Self Enhancement Program on staff nurses’ emotional labor	Emotional Labor Scale ( Brotheridge & Lee, 2002).
Secondary 3	To determine the impact of Integrated Emotional-Self Enhancement Program on staff nurses’ self-compassion	Self-compassion Scale ( Neff, 2003).
Secondary 4	To determine the impact of Integrated Emotional-Self Enhancement Program on staff nurses’ intrinsic motivation	Intrinsic Motivation Assessment Scale (developed by the investigator)
Secondary 5	To examine any change in the patients’ perception of nursing care	Perception of Nursing Care Scale (developed by the investigator)
Secondary 6	To examine any change in the nurse-in-charges’ perception of nursing care.	Perception of Nursing Care Scale (developed by the investigator)

### Data collection

2.9

Data from the staff nurses, patients, and nurse-in-charges will be collected at baseline and 3-month pre-intervention, and immediately after the intervention, at 3-month, and 6-month follow-up by the investigator. Multiple baselines enable an assessment of whether changes occur after or during an intervention, rather than before or as a result of any extraneous factor (
Dundas, Binder, Hansen, & Stige, 2017). The questionnaires will be completed by the participants on the same day. The investigator will always be present with the participants when they fill in the questionnaire and will provide help to understand the questionnaire’s statements if needed. All the participants will be given a unique code to maintain confidentiality and to make sure that only the participants who have consented to participate complete the questionnaires. The investigator will collect the questionnaires on completion and store them safely in a folder. The investigator has considered an attrition rate of 20% while calculating the sample size, to account for participants who discontinue the intervention or follow-ups. Also, the investigator will maintain an attendance sheet of the participants. Reminders will be sent, and calls will be made to the study participants about upcoming and missed sessions.

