### Design

2.2

The current study has a quasi-experimental (one-group) design, which involves staff nurses working in the general wards of a selected hospital. The present study’s design is well suited, keeping in mind the work shifts of staff nurses and the number of staff nurses in the selected hospital. To derive a better understanding of whether intervention on emotional well-being components would affect staff nurses and the perception of patients and nurse-in-charges, the current study has based its concept on Neuman’s System Model and King’s Interacting Systems Theory to design the conceptual framework. Both of these theories have been proven effective in providing guidance for applying the theoretical understanding to practical clinical nursing situations to improve practice (
Montano, 2021;
Shanta & Connoly, 2013).

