### Study intervention

2.7

The IESE Program was developed by the investigator with the help and collaboration of experts from the field of EI, Human Resource Development, Nursing, and Psychology. The investigators’ personal experience working as a mental health nurse and a thorough literature search served as the foundation for need analysis and base for intervention development. Also, before developing the training program, the investigator interacted with a group of nurses from the study setting as well as other hospitals to do a need assessment. The investigator asked them about the factors that induces stress, their emotional experiences and emotional requirements at work, and the ways they handle stressful situations. The investigator also interacted with patients and nurse-in-charges and nursing supervisors of two hospitals to understand what their expectations are from nursing services. This allowed the investigator to identify and understand practices and gaps in real world. By combining the findings from the need assessment, and critical observation the framework of the training program was developed. Drafts of the IESE program was shared among the above mentioned experts several times for their suggestions and modifications were made as suggested before finalizing the content of the program. The program was also pilot tested among 12 staff nurses in a different setting to establish its credibility and assess its effectiveness. The investigator has also taken a hands-on certificate training course on Emotional Intelligence to gain an understanding of Emotional Intelligence techniques under the supervision of experts in the field of Emotional Intelligence from EquiPoise, Maharashtra, which is a certified Emotional Intelligence training institute in India.

The IESE program does not instruct the nurses on how to feel; rather, it encourages the nurses to reflect on their mental and emotional health. The investigator will deliver the program through lectures, Power Point presentations, group activities, situation analysis, videos, worksheets, and workbooks. A booklet will be given to the participants for future reference. These materials will be applied for a copyright by the authors. Hence, they have not been uploaded to an approved repository yet.

The IESE program components are divided into four sessions. An outline of the sessions is provided in
Table 2.

**Table 2. T2:** Table showing outline of the IESE Program.

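### The trainer sits with the nurses while they complete their self-reports, so a response shift that begins with the training cannot be separated from a programme effect

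*Protocol article*

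**What the plan says.** On the programme, section 2.7 says "The IESE Program was developed by the investigator with the help and collaboration of experts", and then "The investigator will deliver the program through lectures, Power Point presentations, group activities" and other teaching methods. Training is eight hours in groups of 5 to 10.

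On measurement, section 2.9 has data collected at both pre-tests and "immediately after the intervention, at 3-month, and 6-month follow-up by the investigator". It continues: "The investigator will always be present with the participants when they fill in the questionnaire and will provide help" with the statements where needed. Afterwards, "The investigator will collect the questionnaires on completion and store them safely in a folder". The article uses one role name for all of this and describes no separate data collector.

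The nurse outcomes (sections 2.8 and 2.10) are four self-completed scales: emotional intelligence, emotional labour, self-compassion and intrinsic motivation. The investigator also wrote the last of these.

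Section 2.2 states: "The current study has a quasi-experimental (one-group) design". Section 2.12 assesses the training by repeated measures ANOVA.

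Two features could serve as safeguards. One is the pair of pre-tests, which section 2.9 justifies as a check on extraneous change. The other is coding: "All the participants will be given a unique code to maintain confidentiality". Section 7 lists the missing control arm and attrition as limitations and presents the repeated pre- and post-tests as a strength that helps reveal the programme's real impact. It does not mention that trainer and data collector are the same.

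**The concern.** If the investigator's presence affected answers equally at all five visits, the effect would cancel in the pre-post change. The relationship is not constant, however. At the two pre-tests the nurses have not yet been trained by this person. At T1, T2 and T3 they answer in front of the person who taught them, on scales that judge that person's programme. Any verbal help given at those visits comes from someone who has since taught emotional intelligence, emotional labour, self-compassion and motivation as session content (Table 2).

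In a single group, a change in how nurses respond that begins with the training enters the estimated effect in full. A significant time effect could then be read as evidence that the programme works. The abstract envisages extensive delivery in hospitals if it is proven effective.

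**Working it through.** **Step 1. Can the stated safeguards isolate the shift?**

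- *Two pre-tests.* They can show drift or retest effects before training. A component that starts when the nurse becomes the data collector's trainee is absent at both pre-tests and can be present at all three post-tests. A programme effect has the same pattern over time.
- *Repeated measures ANOVA in one group.* It tests whether means differ over time. Without a comparison series, it cannot divide a step at the intervention between programme effect and response shift.
- *Unique code.* It is given for confidentiality and to check consent. The same role holds e-mail addresses and telephone numbers (section 2.7), keeps the attendance sheet and takes the form back (section 2.9), and deals at collection with forms that carry a name (section 2.11). The code does not make the nurse anonymous to the trainer.

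**Step 2. Reproduce the plan's own figure (section 2.5).**

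Inputs: SD 12.3, difference 5, two-sided alpha 0.05, power 80%, dropout 20%.

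n = (1.96 + 0.84)² × 12.3² / 5² = 7.84 × 151.29 / 25 = 47.4, so 48. The plan states 50, which is close enough to confirm the method. With dropout, 50 / (1 − 0.2) = 62.5, so 63 as stated. The printed dropout line contains slips (0.3 and 0.2 in the denominators), which do not bear on this point. Recruitment was then raised to 80, and 80 less 20% leaves 64.

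**Step 3. What size of pure response shift would reach significance?**

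Assumptions: no true effect, SD of change 12.3 (as the plan's formula uses it), and one two-sided normal test of mean pre-post change.

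- SE = 12.3 / √n: 12.3 / √80 = 1.375 and 12.3 / √64 = 1.538.
- Smallest observed mean shift with p<0.05 = 1.96 × SE: 1.96 × 1.375 = 2.7 points (0.22 SD) at n=80, and 1.96 × 1.538 = 3.0 points (0.25 SD) at n=64.
- The planned difference of 5 is 5 / 12.3 = 0.41 SD, so 2.7 points is 2.7 / 5 = 54% of it.

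For a true mean shift b, P(reject) = Φ(b/SE − 1.96) + Φ(−b/SE − 1.96):

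| Assumed shift (points) | n=64 | n=80 |
|---|---|---|
| 0 | 5% | 5% |
| 1 | 10% | 11% |
| 2 | 26% | 31% |
| 3 | 50% | 59% |
| 5 | 90% | 95% |

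The documents give no value for b, so the table shows sensitivity and does not estimate the bias.

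**The case against.** The strongest reply is that nothing in the documents shows a shift occurred. The same person attends every visit and explains the purpose and programme to nurses before recruitment (section 2.13), so some pressure to please is already present at both pre-tests and cancels. Help is given only if needed. This stands: what remains is an increment after training, of unknown size.

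A reader might infer that the bias must favour the programme on every nurse outcome. The documents do not support that. For emotional labour the pleasing answer is not even defined: section 6 expects it to fall, while section 1.1 describes it as an essential part of nurse-patient contact and lists it among the things that interventions aim to enhance.

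A reader might also extend the argument to the patient and nurse-in-charge ratings, since the same investigator collects those forms. Section 2.4 says neither group receives the programme, and section 2.6 expects different patients at each contact point. The investigator never becomes their trainer, so the before-after asymmetry is absent.

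The arithmetic has limits as well. Section 2.5 calls 12.3 the population SD of the outcome and names no scale; it cannot describe a self-compassion average scored 1 to 5. SD × √(2(1 − r)) equals the SD only when the correlation r between visits is 0.5. One normal test is not the planned ANOVA.

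Finally, section 7 concedes the missing control arm and says that limitations may obscure the programme's real effect. That covers part of the ground. However, it does not name this source of bias, and it speaks of obscuring an effect rather than possibly producing an apparent one. A control arm alone would not remove the problem if the trainer still sat with trained respondents.

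**Conclusion.** The point holds as a risk to the nurses' four self-report outcomes. It is a stated procedure, not a detail left to an analysis plan, and no analysis can repair how the answers were obtained. The overlap of developer, trainer, helper and form collector is certain from sections 2.7 and 2.9. It is equally clear that the double pre-test and the one-group ANOVA cannot separate a shift beginning with the training from a programme effect.

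The existence, size and direction of such a shift are not known. The thresholds of 2.7 points (n=80) and 3.0 points (n=64) show only that a shift well below the planned difference of 5 could produce significance. They rest on an SD of change of 12.3, no true effect and a single two-sided test. The documents do not support a claim that the results are biased, or that they are biased towards benefit.

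**What to change.** **For this study.** Section 9 reports follow-up complete in May 2022. Leave section 2.9 unchanged as the record of what was done; writing in a different procedure now would misdescribe the data. In section 7, replace the claim that the repeated pre- and post-tests help to reveal the programme's real impact with a statement such as: nurses' self-reports were completed in the presence of the person who trained them, with verbal help available, so pre-post change in these outcomes cannot be separated from response bias. Interpret any significant time effect on the four nurse scales accordingly. The cost is a sentence or two and a narrower conclusion.

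**For data still to be collected or reuse of the protocol.** Use one fixed written item guide, identical at all visits. Have nurses complete the form in private, without the trainer present, and return it coded and sealed to a drop box. This needs envelopes, a box and a one-page guide. The downside is slightly more missing or misread items. It reduces the risk without removing it, because nurses still know that they were trained.

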### Sample size and selection

2.5

For the current study, all staff nurses working in the general wards will have the probability of being selected. At a 20% dropout rate, 80% power, SD of 12.3 (taken after feasibility study), and clinically significant difference of 5, it was calculated that approximately 63 staff nurses should be recruited for the current study. However, to reduce the chances of higher attrition due to the unpredictable nature of the hospital environment, the researchers decided to recruite 80 staff nurses.

$$n=\frac{{\left[Z_{1-\frac{\alpha }{2}}+Z_{1-\beta }\;\right]}^{2}\sigma^{2}}{d^{2}}$$

*n* = minimum sample size required

$Z_{1-\frac{\alpha }{2}}$
 = 1.96 at
*α* = 0.05

$Z_{1-\beta }$
 = 0.84 at 80% power

*σ* = population SD of the outcome variable = 12.3

*d* = clinically significant difference = 5

$$∴n=\frac{{\left(1.96+0.84\right)}^{2}{\left(12.3\right)}^{2}}{5^{2}}=50$$

With 20% drop out rate

$$n*=\frac{n}{1-0.3}\;=\frac{50}{0.2}=63\;\left(\text{approx}.\right)$$

As nurse-in-charges of all the general wards of the selected hospital will be approached for their consent to participate using complete enumeration, a sample size calculation was not performed. Similarly, a sample calculation was not performed for patients, because only those in-patients who will be receiving care from the recruited staff nurses will be approached for their consent to participate in the study.

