Session	Outline of the content	Duration
I	1. Understanding emotions, intelligence and emotional intelligence a. What is emotion? b. Views on emotion: the old and new paradigms c. How are emotions formed? d. The Plutchik model of emotion e. What is intelligence? f. The types of intelligence 2. The concept of Emotional Intelligence a. The importance of emotional intelligence	2 hour
II	1. The neuroscience behind emotional intelligence a. Basic brain structure and their function b. Parts of the brain that are associated with emotions c. Emotional/amygdala hijack 2. GENOS Model of Emotional Intelligence 3. Core components of emotional intelligence skills	2 hours
III	1. Emotional literacy 2. Interpersonal relationship, sympathy and empathy a. Importance of empathy in healthcare b. Effective interpersonal communication techniques 3. Concept of Emotional Labour and Self-Compassion	2 hours
IV	1. Concept of motivation and developing gratitude 2. Management of difficult emotions: anger and stress 3. Management of difficult emotions: anxiety and sadness	2 hours

To provide the IESE program without disrupting the work environment of the hospital, the consented nurses will be divided into smaller groups of 5-10, so that the participants engage in the activities of the training program with more efficiency. Each group will be given the same IESE program in similar setting and using similar techniques. Nurses in each group will complete a total of eight hours of training (two hours each day for four days) at the end of the intervention program. If a participant misses any session, he/she will be accommodated in another group to complete the missed session. The sessions will be made flexible and accommodating. The investigator will make sure that the IESE program does not overlap with the staff nurses’ daily work schedule and hamper the hospital activities or disturb the patients. The nurse-in-charges, staff nurses, and the nurse-supervisors will be informed many weeks prior to starting the program to effectively make the duty roster. The investigator will collect the e-mail address and phone numbers of the participants, for sending reminders about the sessions, and follow-up.
Table 3 shows an overview of the time plan. The project will be implemented from approximately January 2021 to May 2022, with a total duration of 17 months (which includes data collection and intervention implementation).

**Table 3. T3:** Table showing the timeline of the current study.

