### Statistical analysis

2.12

Mean and standard deviation will be used to describe measurement data. Frequencies and percentages will be used to represent count data. Repeated measures ANOVA will be used to analyze the effect of the training program. Chi-square will be used to see if an association between the variables before is after the training program.

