## Strengths and Limitations

7.

One of the major strength of this study is that it has used established theories and models to design the conceptual framework that would guide the study. The investigator has also used established theories and models to design the intervention program which improves the credibility of the study. Another strength of this study is using multiple pre-tests and longitudinal post-test data collection method. This would be helpful in indicating the true impact of the IESE Program. However, a major limitation of the study is that there is no control arm in this quasi-experimental study. The unavailability of similar hospitals in terms of infrastructure, workforce and working schedule did not allow the investigator to select another setting that could work as a control arm. Another limitation could be a higher attrition rate due to the unpredictable nature of any hospital setting. Appropriate measures were taken to control this limitation during the sample size calculation. The investigator will also send reminder e-mails and messages to participants before every follow-up. All limitations can veil the true effect of the program. However, considering the current state of COVID-19 pandemic, where staff nurses and healthcare professionals are scarce in general, and to avoid large gatherings that can put the participants’ health at risk, the investigator believes that the current study design and sample size will suffice the study objectives.

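### Repeated measures ANOVA over five waves drops any nurse missing one score; with 20% attrition and no control arm, the nurse-reported change is biased towards benefit if poor responders leave more often

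*Protocol article*

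**What the plan says.** Under Statistical analysis the protocol article gives one method for the effect: "Repeated measures ANOVA will be used to analyze the effect of the training program". Under Study outcomes, "The secondary objectives/outcomes will be measured using the validated questionnaires at five time-points". Table 3 sets these as two pre-tests (T0 and T-1) and three post-tests (T1 immediately after training, T2 at 3 months, T3 at 6 months).

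Attrition appears in four places:

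- Sample size and selection: "At a 20% dropout rate, 80% power, SD of 12.3 (taken after feasibility study), and clinically significant difference of 5" lead to about 63 nurses, and then "the researchers decided to recruite 80 staff nurses".
- Data collection: "The investigator has considered an attrition rate of 20% while calculating the sample size", "to account for participants who discontinue the intervention or follow-ups". Reminders and calls are planned for upcoming and missed sessions.
- Study intervention: "If a participant misses any session, he/she will be accommodated in another group to complete the missed session".
- Strengths and Limitations: "Another limitation could be a higher attrition rate due to the unpredictable nature of any hospital setting". The answer given there is the sample size calculation plus reminders before follow-up. The same section names the lack of a control arm as a major limitation.

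**The concern.** Classical repeated measures ANOVA needs a complete row per subject. Run on all five waves, it removes a nurse's entire record when one score is missing, so up to four valid scores go with it. The measures in the document protect the number of nurses analysed. They do not make the nurses who remain representative of those enrolled.

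Selective loss is plausible here. The Background describes workload, stress and low motivation among nurses, which could drive leaving and lie close to what the scales measure. In a controlled trial, similar loss in both arms would partly cancel. Here the effect is a within-group change, so any difference between stayers and leavers goes straight into it.

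The point concerns the four nurse-reported outcomes. Patients are a new sample at each wave, so within-person deletion does not arise for them.

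**Working it through.** **The plan's own figure.** Inputs from Sample size and selection: z-values 1.96 and 0.84, SD 12.3, difference 5.

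- n = (1.96 + 0.84)² × 12.3² / 5² = 7.84 × 151.29 / 25 = 47.4, or 48. An exact paired t calculation gives the stated 50.
- 50 / (1 − 0.20) = 62.5, or 63 as stated. (The 0.3 and 0.2 printed in the dropout line do not give 63; that is a separate slip.)
- With 80 recruited and 20% lost, 80 × 0.80 = 64 complete records and power is about 89%. Power is not the problem.

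**Bias by arithmetic.** Bias of the completer mean = share lost × (mean change in completers − mean change in leavers). Take 20% lost and completers changing by the planned 5 points. The leavers' mean is an assumption:

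| Leavers' mean change | Mean over all 80 | Excess in completers |
|---|---|---|
| 0 | 0.8 × 5 + 0.2 × 0 = 4.0 | 1.0 (25%) |
| 2.5 | 0.8 × 5 + 0.2 × 2.5 = 4.5 | 0.5 (11%) |
| 5 | 5.0 | 0 |

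The number recruited does not enter the formula, so over-recruitment cannot change the bias.

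**Bias by simulation.** From the document: 80 nurses, five waves, SD 12.3. Assumed: correlation 0.5 between waves, so the SD of a change is 12.3 × √(2 × 0.5) = 12.3; true gain 5 at every post-test; leaving after T1 with logit = −1.75 − b × (T1 gain − 5)/12.3. About 15% are lost at b = 0 and 19% at b = 1. Change is measured from the later pre-test.

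| b | Complete cases, T1 / T2 / T3 |
|---|---|
| 0 | 5.0 / 5.0 / 5.0 |
| 0.25 | 5.3 / 5.2 / 5.2 |
| 0.5 | 5.9 / 5.6 / 5.5 |
| 1 | 7.0 / 6.0 / 6.0 |

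At b = 1 a likelihood analysis of all observed scores gives 4.9 / 5.0 / 5.0. Repeat runs move these figures by up to about 0.3. At b = 1 the odds of leaving rise about 2.7-fold (e¹) per SD of smaller gain, which is strong dependence. Measured from the mean of both pre-tests, complete cases at b = 1 give 6.5 / 5.5 / 5.5.

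**Where likelihood estimation falls short.** With the same strength of dependence:

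- Nurses lost before T1, as those who leave the study during training would be: complete cases 7.0 / 5.9 / 6.0, likelihood about 6.4 / 5.3 / 5.3.
- Loss driven by the unseen T3 gain: at T3, complete cases 7.1 and likelihood 6.4.

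**False positives.** A related simulation assumed exactly 20% lost, correlation 0.6 between the T1 and T3 changes, and a true change of zero. Complete cases averaged 1.3 to 1.9 points, and a nominal 5% test of the T3 change rejected in 13% to 25% of runs (moderate to strong dependence). With loss unrelated to response it rejected in 5%.

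**Scattered missed visits.** If each visit is missed independently by a share q of nurses (assumed), complete records number 80 × (1 − q)⁵:

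- q = 5%: 80 × 0.774 = 61.9, about 62.
- q = 10%: 80 × 0.590 = 47.2, about 47, below the 50 the plan requires before dropout.

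**The case against.** A reader might infer that the plan removes nurses who stop training. The text does not support this. The sentence under Data collection is a sample-size allowance, not a rule about who is analysed, and the instruments section has the tools given to participants at each time point with no exception for nurses who stopped. It would also be wrong to say that attrition is met only by recruiting more nurses: make-up sessions, reminders and calls are planned, and these should reduce loss.

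Listwise deletion is not written down either. It follows from the named method in its usual form. The article does not say that all five waves enter one model, and imputation before the ANOVA would be compatible with the text. Missing-data rules are often left to a fuller document, so their absence is not the point here. What remains is that the one method named is a poor choice for five waves with a fifth of nurses expected to be lost.

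The size is also open to challenge. The largest figures need strong dependence and a single pre-test as reference. Loss after an observed T1 score is the setting in which likelihood methods must succeed. Both objections stand, which is why the results are given as a range and the limits of the mixed model are shown.

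Finally, a blanket claim of upward bias would be wrong: for emotional labour the Discussion hopes for a decrease, so the direction is towards benefit.

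**Conclusion.** The concern holds as a weakness in the stated analysis, conditional on selective loss. Classical repeated measures ANOVA discards valid scores and, in a one-arm study, overstates benefit on the nurse-reported outcomes if poor responders leave more often. For a true gain of 5 points, the complete-case estimate runs from 5.0 with unrelated loss to about 7.0 at T1 and 6.0 at T2 and T3 with strong dependence. The dependence, the correlation and the timing of loss are assumptions, because the document gives none of them.

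A mixed model on all observed scores restores about 5 when loss depends on scores already recorded. It removes only part of the bias when nurses leave before T1 or when loss depends on unseen scores. The planned retention measures limit loss but do not correct for what remains. The documents do not establish that bias will occur, nor that nurses who stop training will be excluded.

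**What to change.** In the Statistical analysis section, for the nurse-reported outcomes:

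- Replace the repeated measures ANOVA with a linear mixed model: visit as a categorical fixed effect, unstructured covariance, REML, using every observed score.
- State that nurses who missed or stopped sessions are included at every visit at which they were assessed.
- Report the complete-case ANOVA as a sensitivity analysis, together with one that lets loss depend on unseen scores.

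The cost is a few sentences and slightly more analysis work. Mixed models are available in the software named under Data management, and neither new data nor a different sample size is needed. Follow-up ended in May 2022 according to Study status, so the second step can use only assessments that were actually made. The mixed model relies on a missing-at-random assumption, which is why the last sensitivity analysis is needed.
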